## Abstract

**Background:**

Psoriasis is a chronic inflammatory disease that is often associated with a number of somatic and mental comorbidity. Patients with psoriasis show an increased risk of depression and (social) anxiety.

**Objective:**

The aims of this study are 1) to explore the psychosocial distress of patients with psoriasis and to assess their care needs; and 2) to develop a supportive intervention based on the prior results.

**Methods:**

A multi-stage design with four phases combining quantitative and qualitative methodology will be used and conducted in two centers. 1) A scoping review and focus groups will be used to design a questionnaire to assess the psychosocial distress and care needs of the patients. 2) The questionnaire developed in phase 1 will be used in a cross-sectional survey to assess the extent of psychosocial distress and supportive care needs in 400 patients with psoriasis. 3) A systematic review and meta-analysis will be conducted to identify psychosocial and psychoeducational interventions for patients with psoriasis and to describe their effectiveness. 4) Based on the results of the phases 2 and 3 a manualized supportive intervention will be developed and the feasibility and acceptance of the intervention will be assessed.

**Results:**

Currently, phase 1 of the project has been completed and the recruitment for phase 2 has been started. The systematic review and meta-analysis of phase 3 are conducted simultaneously to phase 2 and results are expected soon. Phase 4 has not been started yet.

**Conclusions:**

The expected results of this study will show the extent of psychosocial distress of patients with psoriasis in Germany and supplement previous research with findings about the supportive care needs of this patient group. Moreover, the developed intervention will help to address the psychosocial support needs of patients with psoriasis. Research shows that psychosocial support is strongly needed.

## Introduction

Psoriasis is one of the most common chronic inflammatory skin diseases with a prevalence of 1 to 3 % in western industrial countries. In Germany about 2 million patients are affected [1,2]. The most common type of psoriasis is “psoriasis vulgaris” also called “plaque psoriasis.” It is assumed that about 25% of patients have moderate to severe disease, and a relevant proportion needs a lifelong treatment [3]. Studies indicate that psoriasis often is associated with other medical conditions, especially in severe cases with a long history of the disease [4]. Known comorbidity includes psoriatic arthritis (PsA) [5]; inflammatory bowel disease [6]; cardiovascular disease [7]; and diabetes [8], influencing morbidity and mortality [9,10]. Increased rates of comorbidity are already found in young children and adolescents [11]. In addition to somatic comorbidity psoriasis can be associated with psychosocial stress and mental illness. Patients with psoriasis show an increased risk of depression, anxiety, and suicidal ideation [12-15]. Especially an early onset of psoriasis increases the risk for depression and social anxiety [14,16]. Moreover, alcohol consumption and nicotine abuse seems to be greater in patients with psoriasis than in the general population [17,18].

Reasons for the psychosocial burden of patients with psoriasis are experienced stigmatization in social situations, the workplace, difficulties with body image, self-esteem, and self-concept [14,19-22]. These factors can be substantial components leading to impaired health-related quality of life (HrQoL) [23]. Other predictors of HrQoL impairments are pruritus [24,25], the time needed for daily treatment and treatment dissatisfaction [26]. Accordingly, patients show a large variety of needs related to disease management which go far beyond symptomatic treatment and include a plurality of psychosocial aspects [27].

Research suggests that psychosocial stress is not just a consequence of psoriasis but can also be involved in the exacerbation of the symptoms [28]. Reich et al [29] found that the itch intensity experienced during psoriasis exacerbation correlated positively with stressful events one month earlier. The concept of the “brain-skin-axis” describes the interaction between mental aspects, immune system, and cutaneous inflammation. In patients with psoriasis, psychosocial stress can worsen the condition, which increases disease-associated and experienced stress, impairs quality of life, and increases psychosocial strain and comorbidity [28]. The individual stress reactivity can affect both adherence as well as treatment response [28]. Besides the individual stress reactivity, age, sex, psychosocial, disease-specific, and treatment-specific factors predict the adherence or compliance [30]. Also in a study by Eskin et al, psoriasis patients showed lower scores in social problem-solving skills as well as higher degrees in negative problem orientation and impulsive-careless problem-solving style compared to healthy controls [31], which indicates that those patients might profit from interventions like problem-solving trainings.

For these reasons, current concepts of psoriasis management include screening for mental comorbidity and recommend interdisciplinary teamwork and psychosocial support if applicable [4].

Until now, different reviews subsumed studies on the effects of psychosocial interventions on psoriasis patients. Larsen et al [32] reviewed nine randomized controlled trials (RCTs), quasi-randomized trials, and controlled clinical trials of patient education and self-management interventions on disease severity and HrQoL and found that little evidence is available. They point out that compared with other chronic conditions, only few effective disease-specific tailored educational programs for psoriasis are available [32]. A narrative review found an overall positive effectiveness of existing psychological and/or educational interventions in psoriasis especially in psychological and HrQoL outcomes [33]. However, they stated that the strength of evidence to support the effectiveness of the published interventions was limited due to methodological weakness in the included studies and suggest further research and RCTs to increase validity of intervention studies. Despite a clear need and some existing evidence-based psychosocial treatments, access to psychological and psychosocial interventions within dermatological services remains limited [34]. Moreover, since evidence on psychosocial interventions is still equivocal, it can be concluded that it is important to find out more about the individual information and support needs of these patients to design interventions that are especially tailored to patient preferences. Therefore, the aims of the described study are:

To assess the psychosocial distress of patients with psoriasisTo investigate their needs for information and psychosocial supportTo develop a psychosocial intervention to educate and support psoriasis patientsTo test the feasibility, acceptance and effectiveness of this intervention

## Methods

A multi-stage design with four phases combining quantitative and qualitative methodology will be conducted. It is displayed in Figure 1.

The project will be carried out at Department of Medical Psychology in cooperation with the Institute for Health Services Research in Dermatology and Nursing at the University Medical Center Hamburg-Eppendorf and the Psoriasis Center at the Department of Dermatology of the University Medical Center Schleswig-Holstein Campus Kiel in Germany.

**Figure 1 figure1:**
[figure not shown]
Flow-chart of study phases.

### Phase 1: Questionnaire Development

A scoping review [35] will be conducted to identify measures to assess psychosocial distress in chronic conditions and skin diseases. Measures that focus on mental illnesses, like the Patient Health Questionnaire (PHQ-9) [36,37] to assess depression symptoms, the Generalized Anxiety Disorder 7 (GAD-7) [38] to measure anxiety symptoms or the Somatic Symptom Disorder (SSD-12) [39] to evaluate somatic symptoms will be used. Risk factors as alcohol consumption will be assessed, for example with the Alcohol Use Disorders Identification Test (AUDIT-C) [40]. Moreover, measures to evaluate the information needs and supportive care needs, as well as the utilization of supportive interventions, empowerment, and resources of psoriasis patients will be searched for and included. The study aims to complement the questionnaire with items, to detect patients that are in need for counseling and supportive interventions. Moreover, questions on sociodemographic data will be included.

Based on the results of the scoping review a complete questionnaire will be developed to assess the psychosocial burden of psoriasis patients. Following, two focus groups with n=10 patients with psoriasis in each focus group will be conducted to validate and complement the results of the scoping review.

#### Recruitment of the Patients

The patients will be consecutively recruited during consultations at the Psoriasis Centers of University Medical Center Schleswig-Holstein Campus Kiel and Institute for Health Services Research in Dermatology and Nursing of the University Medical Center Hamburg.

#### Inclusion Criteria

Adult patients (age ≥ 18) will be included. Patients need to be diagnosed with a mild, moderate, or severe psoriasis and need to agree by signing informed consent. Inclusion criteria will be checked from the treating physician, who will also fulfill a short questionnaire on the patients’ clinical data (severity of the psoriasis, presence of psoriasis arthritis or other comorbidity).

#### Focus Groups

One focus group will be conducted at the Psoriasis Center in Kiel and the second at the Department of Medical Psychology in Hamburg. Each focus group is planned to take 120 minutes and patients will receive 50€ for their participation. The main issue of the discussion will be to critically review the developed questionnaire in terms of feasibility and understanding with the patients and to add missing topics regarding information and supportive care needs.

#### Analysis

The focus groups will be recorded and transcribed. The results will show if any adaption of the questionnaire will be necessary or if further items should be developed and included based on the feedback of the patients. The final questionnaire will then be used in a quantitative survey in phase 2.

### Phase 2: Quantitative Survey

The questionnaire developed in phase 1 will be used in a cross-sectional survey to assess the extent of psychosocial distress and supportive care needs in patients with psoriasis.

#### Recruitment of Patients

Participants for phase 2 will be recruited again through consecutive consultations in the two cooperating dermatology centers.

**Figure 2 figure2:**
[figure not shown]
Survey flow-chart for the questionnaire. Calculated with an expected return rate of 40%.

#### Inclusion Criteria

The inclusion criteria are the same as for phase 1.

#### Sample Size

A sample size of N=400 is projected (Figure 2). Based on an expected return rate of 40% we will approach 1.000 patients, 500 per center.

#### Measures

Based on the results of the scoping review in phase 1 we expect to include measures on mental disorders, quality of life, psychosocial distress, health and risk behaviors, information needs and utilization of supportive interventions, needs for supportive care, empowerment, and resources of psoriasis patients. Moreover, sociodemographic data will be assessed. The health status in terms of psoriasis severity and comorbidity will be rated by the treating physician.

#### Analyses

The primary analyses for phase 2 will be descriptive (percentages, means, and standard deviations). The results of this phase will inform the focus of the treatment elements contained within the intervention.

### Phase 3: Systematic Literature Review and Meta-Analyses

To identify which psychosocial and psychoeducational interventions for patients with psoriasis already exist and which are effective, a systematic review will be conducted. The methods and results will be reported in accordance with the Preferred Reporting Items for Systematic Reviews and Meta-Analyses (PRISMA) statement [41]. First a search strategy will be defined followed by an electronic database search in the following databases: Cochrane Central Register of Controlled Trials (CENTRAL), MEDLINE, EMBASE, and PsycINFO. Two independent reviewers will stepwise screen titles, abstracts, and full-texts according to predefined inclusion criteria. Within the title and abstract screening all references that were rated as possibly relevant by one reviewer will be included. In the full-text screening disagreements will be resolved by discussion. In addition to the electronic search reference and citation tracking will be performed with all included references and systematic reviews that dealt with similar questions to check for further relevant references.

Data will be systematically extracted from the included references on the study population, details of the intervention and the outcomes. Furthermore, the risk of bias will be rated for all controlled trials by two independent reviewers according to the Cochrane Handbook for Systematic Reviews of Interventions [42]. Disagreement will be resolved by discussion as well.

For the most relevant patient-reported outcomes a meta-analysis will be performed on all controlled trials that assessed these outcomes. Primary outcome will be HrQoL. Additional outcomes will be chosen depending on whether there will be enough data for a meta-analysis. Furthermore, if the data allows it, subgroup analysis on HrQoL will be performed to compare different aspects of the interventions in their effectiveness.

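### The phase 3 primary HrQoL meta-analysis pools all controlled trials without separating randomised from quasi- or non-randomised designs, and its result helps to choose the intervention type

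*Protocol article*

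**What the plan says.** The section on phase 3 of the protocol article sets the pooling rule: "For the most relevant patient-reported outcomes a meta-analysis will be performed on all controlled trials that assessed these outcomes". The outcome is named next: "Primary outcome will be HrQoL". Studies are screened "according to predefined inclusion criteria", but the article does not reproduce those criteria. Quality is assessed in duplicate: "the risk of bias will be rated for all controlled trials by two independent reviewers", following the Cochrane Handbook. One subgroup analysis is named: "if the data allows it, subgroup analysis on HrQoL will be performed to compare different aspects of the interventions in their effectiveness". None by study design is named. The items listed for extraction are the study population, the intervention details and the outcomes.

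The Introduction describes an earlier review that "reviewed nine randomized controlled trials (RCTs), quasi-randomized trials, and controlled clinical trials". It reports from a second, narrative review that "the strength of evidence to support the effectiveness of the published interventions was limited due to methodological weakness in the included studies", and that this review called for more RCTs.

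The section on intervention development in phase 4 rests the final choice of intervention type (group, individual or internet-based) on two sources: the care needs found in phase 2 and the meta-analysis of phase 3.

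**The concern.** The pooling sentence decides which studies enter the primary estimate, so it is a stated choice and not a detail that an article would leave to a fuller document. If non-randomised comparisons share one pool with randomised trials, the HrQoL estimate mixes effects protected by randomisation with effects that may reflect differences between the groups compared.

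Two things are at stake. The first is the effectiveness statement itself: according to the Discussion, the effects of these interventions have not yet been shown in a meta-analysis, so this would be the first. The second is the comparison of intervention types. Types are compared across trials, so type and design can be confounded. If one type was studied mainly in randomised trials and another largely in non-randomised ones, a difference in design can look like a difference in effectiveness.

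**Working it through.** **Which designs does the rule admit?** The plan states no figure here that could be reproduced, so this step sets the text side by side.

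- The Introduction lists "randomized controlled trials (RCTs), quasi-randomized trials, and controlled clinical trials of patient education" as separate categories and uses the abbreviation RCT when it means randomised. The phase 3 section does not limit its pool to RCTs.
- In the phase 3 section the term controlled trials marks the limit of both the risk-of-bias rating and the pooling. If the screening criteria already admitted only RCTs, that limit would be redundant. The wording suggests a broader included set, with a control group as the only design condition for pooling.
- This is an inference, since the criteria themselves are not shown, but it is the natural reading.

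**What could it do to the estimate?** Let w be the pooling weight of non-randomised trials and b their mean excess effect in SMD units. Then

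pooled effect = randomised effect + w × b.

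Neither w nor b is in the documents. All values below are assumptions, used only to show scale.

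| Randomised effect | w | b | Pooled effect | Relative shift |
|---|---|---|---|---|
| 0.30 | 0.3 | 0.2 | 0.30 + 0.06 = 0.36 | 0.06/0.30 = 20% |
| 0.30 | 0.5 | 0.3 | 0.30 + 0.15 = 0.45 | 0.15/0.30 = 50% |
| 0.20 | 0.3 | 0.2 | 0.20 + 0.06 = 0.26 | 0.06/0.20 = 30% |
| 0.20 | 0.5 | 0.3 | 0.20 + 0.15 = 0.35 | 0.15/0.20 = 75% |

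Over a wider range, with w from 0.2 to 0.5 and b from 0.1 to 0.4, the shift runs from 0.2 × 0.1 = 0.02 to 0.5 × 0.4 = 0.20 SMD. With w = 0 or b = 0 there is no shift, and with negative b it reverses sign.

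**What could it do to the choice of type?** A shift w × b that is equal in all types leaves their ranking unchanged. Only a difference in shift matters: type B overtakes a truly better type A when

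(w × b in B) − (w × b in A) > true effect of A − true effect of B.

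Illustration, again with assumed values: type A has a true SMD of 0.30 and only randomised trials, so it pools to 0.30. Type B has a true SMD of 0.25 and half its weight from non-randomised trials with b = 0.20, so it pools to 0.25 + 0.5 × 0.20 = 0.35. The differential shift of 0.10 exceeds the true gap of 0.05, and the ranking reverses.

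**The case against.** The case against has several parts.

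1. *The eligibility criteria are not shown and might restrict the review to RCTs.* This stands as a caveat. The trial types in the Introduction describe what one earlier review of nine studies covered, and the article does not say how many were non-randomised. Nor does it say that the methodological weakness it reports was lack of randomisation. The natural reading still admits all controlled designs.

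2. *A reader might infer that the risk-of-bias ratings go unused.* The article does not support that. It states no use for them in the synthesis, but this is commonly left to the full review protocol, and silence is not a decision.

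3. *A reader might infer that the pooled effect alone selects the intervention.* It does not. The phase 2 needs data count as well, and the draft is revised after the expert focus group and the think-aloud sessions. However, those steps address content, acceptability and usability, not comparative effectiveness. The pilot of about 30 randomised participants cannot correct a wrong choice either, since the authors expect too little power to detect meaningful differences reliably.

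4. *Uniform inflation does not change a ranking.* This is correct, and it is why the point is limited to bias that differs between types. Nothing in the article ensures that such bias is equal across them.

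5. *Evidence is scarce, and a primary pool of RCTs only could leave too few trials for the subgroup comparison.* This stands, and it argues for stratified presentation rather than outright exclusion.

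**Conclusion.** The point holds in a limited form. The article commits the primary HrQoL meta-analysis to all controlled trials with no separation by randomisation, in a literature it describes as weak, and the result contributes to the choice of intervention type. If bias from non-randomised trials differs between types, the comparison could be distorted.

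The size and direction are unknown. The 20% to 75% inflation and the reversed ranking follow only from the assumed weights and biases and are not estimates for this review. The conclusion rests on one reading, that the term controlled trials includes quasi- and non-randomised designs. If the unseen criteria admit only RCTs, the point reduces to a clarification of wording. It is a cheap improvement to the analysis and does not show that the planned estimate is wrong.

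**What to change.** - State whether quasi- and non-randomised controlled trials are eligible for pooling.
- Add study design to the extraction items.
- Stratify the HrQoL meta-analysis, and any subgroup comparison of intervention types, by randomised versus non-randomised design, with quasi-randomised trials in the second stratum.
- Make the randomised stratum the main basis for effectiveness statements and for what the meta-analysis contributes to the choice of type. Show the pool of all controlled trials alongside it.
- Name a sensitivity analysis that excludes trials at high risk of bias, using the ratings already planned.

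The cost is one more extracted item, a few sentences and additional forest plots. The downside is fewer trials and a wider interval in the randomised stratum, and possibly too few trials for some subgroups; where that happens, it should be reported as such. The Results section says the review is under way with completion expected soon, so the change should be made and dated before pooled results are seen, or declared as made afterwards.

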#### Phase 4: Intervention Development and Assessment of Feasibility

Based on the results of the phases 2 and 3 a supportive intervention will be developed.

#### Intervention Development

Based on the needs assessment and the meta-analyses an intervention will be developed addressing the needs of the patients with the most promising intervention type, which can be face-to-face in a group or single setting or an internet-based approach. Internet-based interventions may reach larger parts of the patient population and allow a high degree of flexibility. Existing Internet-based programs (eg, for depression, alcohol consumption, or stress reduction) could be adapted for these patients or certain modules could be tailored [43,44]. Furthermore, barriers such as privacy concerns and fear of being stigmatized could be overcome by the anonymity of Internet-based interventions. Systematic reviews show favorable effects of Internet-based (cognitive behavioral) interventions for chronic somatic conditions [45,46], but research in dermatological conditions is rare [47]. However, a final decision about the type of intervention will be based on the patients care needs explored in phase 2 and the results of the meta-analysis in phase 3.

We plan to use qualitative methods to explore how professionals and people with psoriasis view the draft of the intervention. In the first step, a focus group with 6 health care professionals (four dermatologists and two psychologists) and 2 patient representatives (eg, of the “Deutscher Psoriasis Bund e.V.” [48] or self-help groups organized in Internet forums) are planned to discuss the developed intervention. The participants will be presented the intervention materials and asked to comment on content, acceptability, and usability. The experts will also be asked to discuss where in treatment procedure the intervention is most useful and realizable. The focus groups will be recorded and transcribed.

In the second step, n=8 patients with psoriasis will be sought using convenience sampling recruited from the participating clinics. Think aloud methodology [49] will be used, whereby participants will be asked to detail their ‘live’ reactions on the content and layout of the intervention. Patients will be encouraged to voice their views on all aspects of the intervention including likely usefulness of the content, appearance of the content, feasibility of following the advice etc. The intervention will be modified on the basis of these qualitative results.

